#### Longitudinal cohort

2.3.2

Core Activity 2 will include a prospective observational longitudinal cohort of WLHIV and their liveborn infants (*n* = 450). Approximately half of WLHIV in CA2 will be WLHIV who intend to breastfeed or are breastfeeding at enrollment. Study visits will be conducted at entry and 6 (+/−2), 20 (+/−4), and 48 (+/−4) weeks post-birth for all participants. Breastfeeding WLHIV-infant dyads will complete additional study visits at 7 (+/−7) days post birth, at the time of any breastfeeding complications, and at weaning (Figure 3). Complication visits will be triggered by a plasma viral load of >50 copies/mL for the WLHIV and/or a breast problem, including painful breast swelling, red or shiny skin, cracked or bleeding nipples, blocked ducts, abscess, rash or dermatitis, with or without associated fever. Participants will be instructed to notify site staff immediately when symptoms of a breast problem occur so that a complication visit can be scheduled in a timely fashion. All participants will be followed until infant HIV testing is complete and at least 48 weeks post-birth. Participants who have completed infant HIV testing by 48 weeks post-birth will exit the study at 48 weeks. Breastfeeding participants who have not completed infant HIV testing by 48 weeks post-birth will exit the study at 24 weeks after the infant's last exposure to breast milk, or at 96 weeks post-birth, whichever comes first.

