#### Core Activity 2 quantitative analysis

2.3.7

In order to describe infant feeding practices and identify aspects of clinical, behavioral, and social factors associated with different infant feeding choices and durations among WLHIV (CA2 co-primary objective), we will describe infant feeding among CA2 participants in several ways. Participants will be categorized by infant feeding method: breastfeeding (defined as receiving breast milk from the mother with HIV for any duration) and replacement feeding (defined as no exposure to breast milk from the mother with HIV). We will report the number and proportion of women who initiate breastfeeding among those who intended to breastfeed, and those who complete their intended duration of breastfeeding.

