Several baseline factors will be evaluated as predictor variables to explore factors associated with type of infant feeding. These baseline factors include: geographic location (site); year enrolled; demographic factors (race, ethnicity, age, internationally born, language, marital status); clinical factors (gravity/parity, timing of HIV diagnosis, viral load, CD4 count, ART adherence); social and structural determinants of health (education, employment, income, housing, food insecurity, transportation); healthcare access; health literacy; HIV disclosure; HIV-related stigma; interpersonal violence; substance use; and depression/anxiety symptoms. Three different logistic regression models will be used to identify the statistically significant baseline factors that are associated with the binary outcomes: breastfeeding vs. replacement feeding, exclusive breastfeeding vs. exclusive replacement feeding, and whether a participant completes their intended duration of breastfeeding. Additionally, a generalized linear regression model will be used to determine the baseline factors associated with the continuous outcome, duration of breastfeeding. No adjustments for multiple comparisons are planned. For each model, the marginal regression for each factor will be applied to screen for significant factors first, and then the best subset regression variable selection approach will be used to determine the significant factors in the regression model. For linear regression models, standard diagnostic procedures will be conducted to evaluate key model assumptions, including linearity of covariate effects, normality of residuals, homoscedasticity, independence of observations, and the absence of influential outliers. Linearity will be assessed using various plots and summary diagnostics, and homoscedasticity through residual scatterplots and formal tests when appropriate. For logistic regression models, assumptions will include correct specification of the logit link, linearity of continuous covariates on the log-odds scale, absence of multicollinearity, and lack of overly influential observations; these will be assessed using diagnostic plots, variance inflation factors, and influence measures such as delta-beta statistics. If assumption violations are identified, prespecified corrective actions will be implemented.

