Missingness of data will be summarized by groups and key covariates, and graphical and tabular diagnostics will be used to assess whether data are plausibly missing completely at random (MCAR), missing at random (MAR), or missing not at random (MNAR). For the primary analyses, regression models will be fit using methods appropriate to the assumed missingness mechanism, with complete-case analysis applied only when missingness is minimal and unlikely to introduce bias. When missing data are non-negligible, multiple imputation using fully conditional specification will be employed.

We will describe the proportion of milk samples among breastfeeding participants that contain detectable HIV RNA and DNA (co-primary objective). Also, we will use mixed effects logistic regression models to identify statistically significant factors associated with detectable HIV in milk. These will include baseline and other factors including time of sample collection (i.e., study visit); presence of mastitis; presence of nipple trauma; presence of mixed feeding; and presence of plasma viremia in plasma sample collected per standard of care nearest (and within +/- 14 days) to the date of milk sample collection.

We will use logistic and generalized linear regression models to determine whether infant feeding method is associated with maternal mental health and quality of life survey scores, decision regret, satisfaction with infant feeding choice, and infant growth and development, and to identify factors associated with detectable plasma viral load. The temporal relationship between detectable HIV in breast milk and in plasma will also be described (secondary objectives).

Transmission of HIV to infants via breastfeeding is unlikely to occur in this study given the low risk of transmission among WLHIV on ART with sustained viral suppression, the close monitoring and regular follow up of participants in a research study, and the sample size of anticipated breastfeeding WLHIV. We will describe any infant HIV transmissions, including the maternal plasma viral load and presence of detectable HIV in milk, along with additional data gathered from FIMR-HIV review (exploratory objective).

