#### Power calculation

2.3.8

Sample size was determined using the primary objective of CA2 to determine which baseline factors are significantly associated with the decision to breastfeed among postpartum WLHIV. Assuming that the proportion of WLHIV who breastfeed is 150 among 450 recruited participants and a 5% loss to follow-up rate, we calculated that the minimum detectable odds ratio (MDOR) for detecting an association between breastfeeding and continuous exploratory variables would be 1.34 for each 1 standard deviation increase (with 80% power and a significance level of 0.05 for a two-sided test). For a binary explanatory variable with a Binomial distribution where π = 0.5, the MDOR is 1.75 (86, 87). Since the analysis uses logistic regression to evaluate associations between baseline factors and a binary outcome, the odds ratio is the natural measure of effect size. The true effect sizes of exploratory predictors are unknown *a priori*, so the MDOR provides a transparent way to quantify the smallest association that can be detected with 80% power at a two-sided *α* = 0.05, given the anticipated event rate, sample size, and predictor distribution. Thus, MDOR reflects the statistical sensitivity of the study and aligns directly with the planned modeling framework.

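### Breastfeeding duration is modelled as a fully observed continuous outcome, although loss to follow-up and the 96-week exit leave some durations known only as a lower bound

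*Protocol article*

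**What the plan says.** Section 2.3.7 (Core Activity 2 quantitative analysis) places the factors associated with feeding choices and durations in a CA2 co-primary objective. For duration, "a generalized linear regression model will be used to determine the baseline factors associated with the continuous outcome, duration of breastfeeding". The checks listed for linear models include "normality of residuals, homoscedasticity, independence of observations, and the absence of influential outliers"; none of the listed checks concerns incomplete durations. A separate logistic model addresses "whether a participant completes their intended duration of breastfeeding".

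On missing data, the same section allows complete-case analysis only when missingness is minimal and unlikely to bias. Beyond that, "When missing data are non-negligible, multiple imputation using fully conditional specification will be employed".

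Section 2.3.2 (Longitudinal cohort) sets the follow-up. "Participants who have completed infant HIV testing by 48 weeks post-birth will exit the study at 48 weeks". Breastfeeding participants whose infant testing is not complete by then leave 24 weeks after the infant's last breast milk exposure, "or at 96 weeks post-birth, whichever comes first". Section 2.3.8 (Power calculation) assumes "a 5% loss to follow-up rate".

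No censoring or time-to-event method appears in the article.

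**The concern.** Weaning is an event in time. If a woman leaves the study while breastfeeding, her duration is known to exceed the time last seen and no more. A generalized linear model for a continuous outcome needs one number per woman. Three routes are open under the text: drop her, enter last contact as if it were weaning, or impute her duration as an ordinary missing value. None uses the known minimum.

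The error is not random with respect to the outcome. Women who breastfeed longer are exposed to loss for longer, so long durations are cut short or removed more often than short ones. Loss may also differ by predictor level. The Introduction describes postpartum lapses in care linked to insurance changes and care transitions, and healthcare access, income, housing and transportation are among the candidate predictors. Because predictors are screened by significance without multiplicity adjustment, an artefact of unequal loss could be reported as a factor associated with duration.

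The completion outcome has the same gap: a woman lost before her intended duration has an unknown result, not a failure.

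**Working it through.** **The plan's own figures.** The article gives no figure for the duration analysis. Its minimum detectable odds ratios concern feeding choice. With n = 450 × 0.95 ≈ 427 and p = 150/450 = 1/3, the continuous-predictor formula exp(√[(1.960 + 0.842)² / (n·p·(1 − p))]) gives 1.333, against 1.34 stated. For a binary predictor, the Wald variance of the log odds ratio with a breastfeeding proportion of 1/3 in the unexposed gives 1.750, against 1.75 stated. Neither depends on how duration is analysed.

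**Assumptions for the size of the bias.** From the article: 150 breastfeeding women, 5% loss, 96-week limit. Assumed: Weibull durations (shape 1 or 1.5), median 12, 24 or 36 weeks in the reference group, a binary factor that multiplies duration by 1.5, and loss at a constant rate reaching the stated percentage by week 48. The target is mean weeks breastfed up to week 96, so a woman still breastfeeding at week 96 has the known value 96 and only loss censors.

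**One case in closed form (shape 1, median 24).** Weaning rates are λ₀ = ln 2/24 = 0.02888 and λ₁ = ln 2/36 = 0.01925. The loss rate is μ = −ln(1 − loss)/48, which is 0.00107 for 5% and 0.00465 for 20%. Mean recorded weeks, with last contact entered as weaning, are (1 − e^(−96(λ+μ)))/(λ+μ).

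| Loss, reference / factor | Reference mean | Factor mean | Difference | Against truth |
|---|---|---|---|---|
| none (truth) | 32.46 | 43.76 | 11.30 | – |
| 5% / 5% | 31.51 | 42.21 | 10.71 | −5% |
| 15% / 15% | 29.59 | 39.14 | 9.55 | −15% |
| 5% / 20% | 31.51 | 37.62 | 6.11 | −46% |
| 20% / 5% | 28.63 | 42.21 | 13.58 | +20% |

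The last row shows that unequal loss can also inflate an effect. The direction depends on which group loses more women.

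**Simulation over all six shape and median combinations.**

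| Loss | Effect, last contact as weaning |
|---|---|
| 5% in both groups | 2% to 6% low |
| 15% in both groups | 8% to 17% low |
| 5% reference, 20% factor | 18% to 61% low |

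At 5% loss in both groups, 2% to 5% of women are lost while still breastfeeding and mean duration is 1% to 4% low. The Kaplan-Meier restricted mean recovered the true difference within about 1%.

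**Does imputation repair it?** Durations of lost women were imputed from women of the same factor level with known duration, ignoring the lower bound. At shape 1, median 24 and 5% versus 20% loss, the simulated true difference was 11.4 weeks. Last contact as weaning gave 6.1, imputation 7.4 and Kaplan-Meier 11.3. Imputation removes only part of the bias.

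**No true effect (shape 1, medians 24 and 36).** With 5% versus 20% loss and last contact as weaning, type I error was 11% and 14% instead of 5%. With 5% in both groups it was 5.4% and 5.8%.

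**The 96-week limit.** If the target is full, uncapped duration, 0% to 22% of women are still breastfeeding at exit, and entering 96 as their final value lowers the effect by 0% to 7% at median 12, 7% to 34% at median 24 and 27% to 55% at median 36.

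**The case against.** The strongest reply is that the effect is small on the article's own figures. At 5% loss unrelated to the predictors, 2% to 6% attenuation would not change a conclusion. The design also follows most breastfeeding women past weaning and adds a weaning visit, and the 96-week limit touches only women breastfeeding for about 22 months. All of this stands. But the 5% enters a calculation about feeding choice, which is known soon after birth, whereas duration requires observation until weaning.

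A second reply is that section 2.3.7 promises methods suited to the missingness mechanism, and the analysis plan may say how duration is imputed. This stands in part: an imputation that respects the lower bound would be acceptable. The article does not say so, and it fixes the model as one for a continuous outcome.

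Some stronger readings are tempting but not supported:

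- A reader might infer attenuation of a quarter or more at 5% loss. Take exponential durations with means of 16 and 32 weeks. The true difference to week 96 is 30.41 − 15.96 = 14.4 weeks. Deleting every woman without an observed weaning date gives about 11.0 (−24%). With no loss at all, deleting only those still breastfeeding at week 96 already gives 26.97 − 15.76 = 11.2 (−22%). Most of that figure therefore comes from discarding values which the 96-week target treats as known. Entering last contact as weaning at 5% loss gives 29.55 − 15.70 = 13.9 (−4%).
- A reader might infer that the 48-week exit also censors duration. It applies to women whose infant testing is complete, which suggests that they have weaned.
- A reader might infer that the completion model is wrong unless intended duration is forced in. Meeting one's own goal is a legitimate outcome, and conditioning on the goal asks a different question. Statisticians could reasonably disagree, and the article does not show that any factor would take the wrong sign.

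**Conclusion.** The point holds as a mismatch between outcome and model. The article builds right-censoring into follow-up, then names a model and missing-data rules that do not use partly observed durations, for an analysis within a co-primary objective.

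The size is conditional, because the article gives no distribution of durations and no pattern of loss. The bias is minor at 5% loss that is equal across predictor levels, moderate at 15%, and material if loss differs by predictor level, if women still breastfeeding at 96 weeks are dropped, or if full duration is the target and durations are long. The 18% to 61% range assumes the heavier loss falls on the longer-feeding group; the reverse pattern would exaggerate the effect. The completion outcome shares the problem only for women lost before their goal.

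**What to change.** Among women who start breastfeeding, analyse time from birth to last breast milk exposure. Use Kaplan-Meier curves with a Cox or accelerated failure time model, or the restricted mean to 96 weeks, and censor at last contact or week 96. State whether the target is duration up to 96 weeks or full duration.

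For completion of intended duration, treat women lost before their goal as censored, for example through censoring weights, rather than as failures or exclusions. A version adjusted for intended duration may be added as a sensitivity analysis.

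The cost is analysis-plan wording. The planned visits and feeding histories will supply weaning and last-contact dates. Sample size, visits and the stated minimum detectable odds ratios do not change.

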#### Breast milk specimen collection

2.3.5

Breast milk samples will be collected at each study visit from breastfeeding participants until weaning is complete. Milk will be expressed from both breasts according to participants’ preferred method, which may include hand-expression or the use of a manual or electric breast pump. A minimum of 15 mL and maximum of 60 mL of breast milk will be collected at most visits, with smaller minimum and maximum volumes allowable in the first 14 days postpartum, when the milk supply is not yet established. Milk will be refrigerated immediately and processed within 6 h of collection. Milk will be centrifuged and the fat layer discarded. The aqueous layer of milk will be aliquoted and cryopreserved. Breast milk cells will be cryopreserved as a nonviable cell pellet. Breast milk samples will be shipped to a centralized laboratory for batched analysis. HIV RNA will be measured in the aqueous milk compartment and HIV DNA will be measured in the breast milk cells using quantitative PCR. Results of breast milk HIV testing will not be shared with sites nor participants, because the assays will not be performed in real time, and the research assays are not approved for clinical use.

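### The described proportion of milk samples with detectable HIV mixes scheduled samples with samples prompted by viremia or breast problems, so it would tend to overstate detection at scheduled visits

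*Protocol article*

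**What the plan says.** Three parts of the protocol article bear on this.

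- **Sampling frame (2.3.5, Breast milk specimen collection):** "Breast milk samples will be collected at each study visit from breastfeeding participants until weaning is complete".
- **Which visits those are (2.3.2, Longitudinal cohort):** all participants are seen at entry and at 6, 20 and 48 weeks after birth. Breastfeeding dyads have additional study visits at about day 7, "at the time of any breastfeeding complications, and at weaning". The same section adds: "Complication visits will be triggered by a plasma viral load of >50 copies/mL for the WLHIV and/or a breast problem".
- **Analysis (2.3.7, Core Activity 2 quantitative analysis):** "We will describe the proportion of milk samples among breastfeeding participants that contain detectable HIV RNA and DNA", which the section tags as co-primary. Nothing here separates scheduled from triggered samples. The mixed effects logistic model then lists "time of sample collection (i.e., study visit); presence of mastitis; presence of nipple trauma; presence of mixed feeding", together with "presence of plasma viremia in plasma sample collected per standard of care nearest" to the milk sample and within 14 days of it.

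Section 2.3.8 (Power calculation) supplies the plan's own expectations. About 5% of women on modern treatment would have detectable RNA in milk, 10%–15% of those who breastfeed would have mastitis, and detection would be 50% with mastitis against 5% without.

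**The concern.** A proportion of samples is a fair measure of how often milk contains virus only if the reason for taking a sample is unrelated to the result. Here some samples exist because the woman was viremic or had a breast problem, and the plan expects mastitis, at least, to raise detection tenfold. Counting those samples equally with scheduled ones pulls the proportion upward. The result is neither a prevalence at a given visit nor a prevalence among women.

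The figure would also depend on site practice. Plasma is tested under local standard of care, the Introduction reports wide variation between institutions in viral load monitoring, and breast-problem visits depend on women contacting staff. A site that tests or hears more would add more high-risk samples with no difference in milk virology.

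Section 2.3.8 says that no prevalence data exist for milk on integrase inhibitor-based treatment and that detection in milk is the study's proxy for transmission risk. The figure is therefore likely to be cited on its own.

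**Working it through.** **1. The plan's power figure.** Inputs from section 2.3.8: 150 breastfeeding women, 10%–15% with mastitis, 50% against 5%, significance level 0.05 (taken as two-sided). The formula is

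power = Φ{ [|p1 − p2| − 1.96·√(p̄(1 − p̄)(1/n1 + 1/n2))] / √(p1(1 − p1)/n1 + p2(1 − p2)/n2) }.

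For 15 against 135 women, p̄ = (7.5 + 6.75)/150 = 0.095. The null term is 1.96 × 0.0798 = 0.156 and the alternative standard error is 0.130. Power is Φ(0.294/0.130), about 98.8%. For 22–23 against 127–128 women it is 99.8%. The stated 98%–99% is reproduced to within a point. It compares women with and without mastitis, so the point below does not touch it.

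**2. Pooled proportion.** Let each of 150 women give k scheduled samples at 5%, and let a fraction f give one triggered sample at positivity q:

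pooled = (150·k·0.05 + 150·f·q) / (150·k + 150·f).

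From the document: 150, 5%, f = 10%–15%, q = 50%. Assumed: k = 2 or 4 (women wean at different times), one triggered sample per affected woman, and 5% applied per scheduled sample.

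| k | f | q | Calculation | Pooled | Ratio to 5% |
|---|---|---|---|---|---|
| 4 | 10% | 50% | (30 + 7.5)/615 | 6.10% | 1.22 |
| 4 | 15% | 50% | (30 + 11.25)/622.5 | 6.63% | 1.33 |
| 2 | 10% | 50% | (15 + 7.5)/315 | 7.14% | 1.43 |
| 2 | 15% | 50% | (15 + 11.25)/322.5 | 8.14% | 1.63 |

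**3. Sensitivity to inputs that the document does not give.**

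- Triggered positivity of 20% (assumed): (30 + 3)/615 = 5.37% with k = 4 and f = 10%, up to (15 + 4.5)/322.5 = 6.05% with k = 2 and f = 15%.
- Triggered positivity of 5%: the pooled figure stays at 5.0%, with no inflation.
- Triggered samples from 30% of women at 50% (assumed, to allow for viremia and other triggers): (30 + 22.5)/645 = 8.1% with k = 4, and (15 + 22.5)/345 = 10.9% with k = 2.

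**4. The visit covariate.** A simulation used 150 women with four scheduled visits each and 5% detection when neither mastitis nor viremia was present. The odds ratio was 19 for each of these, which corresponds to 50% against 5%. Complication visits occurred for mastitis (12.5% of women), other breast problems (15%) and viremia (10%). Mastitis was present at 1% of scheduled visits and viremia at 2%. All these frequencies are assumptions, and the fitted model was a logistic regression without a random effect. The true log odds ratio for mastitis was ln 19 = 2.94. Median estimates over 1,000 runs were 2.96 (standard error 0.46) without visit labels and 3.04 (standard error 0.61) with labels that include a complication level. The estimate barely moves. The standard error rises by 0.61/0.46, about one third.

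**The case against.** The strongest reply is that Table 3 lists the co-primary objective as identifying factors associated with detectable HIV in milk, not as estimating prevalence. For that objective, sampling during mastitis and viremia is a strength, because it supplies the exposed observations. This stands, and no triggered sample should be dropped from the model. It does not remove the point, since section 2.3.7 names the sample proportion as a quantity to be described and tags it as co-primary.

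A second reply is that tabulation by visit type and clustered intervals are commonly left to a fuller document. That is fair as to missing detail. But the article does fix the unit (milk samples) and the frame (every study visit), and together these define the enriched figure.

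Third, the size rests on assumptions. The 50% derives from a pre-treatment-era effect, and no frequency or positivity is given for viremia-triggered samples. This stands and limits the claim to a range.

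A reader might also infer that coding time as study visit biases the mastitis effect. The documents do not support this:

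- The article does not say that complication is a level of the variable.
- Mastitis, nipple trauma and plasma viremia are separate covariates.
- Many other breast problems trigger a visit, so non-mastitis complication samples need not come mainly from viremic women.
- The simulation shows lost precision with little bias. Only if mastitis were seen solely at complication visits would its contrast rest entirely on other complication samples.

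Nor does repeated sampling by itself push a proportion upward. It affects the confidence interval.

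**Conclusion.** The point holds for the descriptive proportion. Read as written, it includes samples selected on conditions that the plan expects to raise detection. On the plan's own mastitis figures, with two to four scheduled samples per woman and one triggered sample per affected woman, the pooled figure is about 1.2 to 1.6 times the scheduled-visit value (6.1%–8.1% against 5%). It is 5.4%–6.0% if triggered positivity is only 20%, and there is no inflation if triggered samples are no more often positive. That last case contradicts the plan's power premise. Adding viremia-triggered samples could take it to about twice the scheduled value, but only on inputs that the document does not supply.

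For the regression, what remains concerns precision and clarity: an unscheduled sample has no defined place on a visit-coded time scale. Neither a wrong mastitis effect nor a fault in the power figure is shown. This is a worthwhile, nearly free improvement, not a flaw that undermines the co-primary association analysis.

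**What to change.** In section 2.3.7, define the descriptive proportion on milk from the scheduled visits (day 7 and weeks 6, 20 and 48). Report it per visit and per woman, with confidence intervals that allow for several samples from one woman. Report complication-visit samples separately, by trigger (viremia or breast problem). Report weaning-visit samples separately too, since their timing varies and the Introduction lists abrupt weaning among the traditional risk scenarios.

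In the mixed model, keep all samples and enter time as weeks since birth instead of a visit label.

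The cost is analysis wording. No new samples or visits are needed. The main figure rests on fewer samples: leaving out triggered ones removes between 15/615 = 2.4% and 22.5/322.5 = 7.0% of the total in the mastitis-only cases above, plus any weaning samples.

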#### Core Activity 2 objectives

2.3.1

The primary, secondary, and exploratory objectives of CA2 are presented in Table 3.

**Table 3 T3:** Objectives of Core Activity two.

Objective Type	Objective
Primary	Describe infant feeding practices and identify aspects of clinical, behavioral, and social factors associated with different infant feeding choices and durations among WLHIV
	Identify factors associated with detectable HIV RNA or DNA in breast milk
Secondary	Describe key outcomes among WLHIV according to infant feeding choice
	Describe key outcomes among infants of WLHIV according to infant feeding choice
	Determine the costs and cost-effectiveness of different infant feeding choices
	Identify factors associated with detectable HIV RNA in the plasma of WLHIV who breastfeed
	Describe the temporal relationships between detectable HIV DNA or RNA in breast milk and detectable plasma HIV RNA among WLHIV
Exploratory	Explore risk factors for infant HIV acquisition during breastfeeding

WLHIV, woman living with HIV.

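### Detectable plasma viral load, a result that recurs within a woman, is assigned logistic regression with no term for repeated results, while the milk outcome gets a mixed model

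*Protocol article*

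**What the plan says.** Table 3 (section 2.3.1) lists as a secondary objective: "Identify factors associated with detectable HIV RNA in the plasma of WLHIV who breastfeed". Section 2.3.7 covers it in a sentence that begins "We will use logistic and generalized linear regression models to determine whether infant feeding method is associated with", runs through several maternal and infant outcomes, and ends "to identify factors associated with detectable plasma viral load". That sentence names no random effect, GEE or clustered standard error. The paragraph on milk in the same section reads "we will use mixed effects logistic regression models to identify statistically significant factors associated with detectable HIV in milk".

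Three statements bear on how often plasma is measured:

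- As a covariate in the milk model, plasma viremia is taken from the "plasma sample collected per standard of care nearest (and within +/- 14 days) to the date of milk sample collection".
- Section 2.3.2 sets the schedule for all participants: "Study visits will be conducted at entry and 6 (+/−2), 20 (+/−4), and 48 (+/−4) weeks post-birth". Breastfeeding dyads have further visits at about day 7, at complications and at weaning.
- The same section says "Complication visits will be triggered by a plasma viral load of >50 copies/mL for the WLHIV and/or a breast problem".

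Section 2.3.7 also plans to describe how milk and plasma detection relate over time. That requires serial plasma results.

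**The concern.** Two outcomes in the same women are both binary and both measured repeatedly. One gets a model for repeated measures and the other does not. The phrase 'generalized linear' does not close the gap, because the same section uses it for breastfeeding duration, which has one value per woman. The listed diagnostics would not catch the problem either: independence of observations is a check for the linear models but is not listed for the logistic ones.

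What goes wrong depends on how the rows are built. With one row per plasma result, standard errors for woman-level factors such as housing, stigma or education are too small, and chance associations are declared significant. With one ever-detectable indicator per woman, the outcome grows with the number of tests and the length of follow-up. Whatever leads to closer monitoring or longer breastfeeding then looks like a risk factor for viremia. The Introduction itself reports wide variation between institutions in viral load monitoring.

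**Working it through.** The article gives no sample size, power or precision for the plasma outcome, so there is no stated figure to reproduce.

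**Inputs.** From the article: two-sided alpha 0.05 and 150 breastfeeding women (section 2.3.8). Assumed, because the article gives none: m = 4 plasma results per woman (8 for a more closely tested woman), ICC 0.1 to 0.5, and 3% detection per test for the ever-detectable calculation.

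**Reading A: one row per result, woman-level factor.** Design effect DE = 1 + (m − 1) × ICC. The true size of a nominal 5% test is 2 × Φ(−1.96/√DE). With m = 4:

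| ICC | DE | True SE / naive SE = √DE | True type I error |
|---|---|---|---|
| 0.1 | 1.3 | 1.14 | 8.6% |
| 0.3 | 1.9 | 1.38 | 15.5% |
| 0.5 | 2.5 | 1.58 | 21.5% |

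A simulation of 150 women with 4 beta-binomial results each, a null binary woman-level factor, per-test detection of 5%, 10% or 20%, and about 1,500 runs per setting agrees. The naive logistic test rejected in 7.5–9.0% of runs at ICC 0.1, 15.1–15.5% at 0.3 and 21.1–22.7% at 0.5. Cluster-robust errors on the same data gave 4.5–6.3%.

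This direction holds for woman-level factors. For factors that vary within a woman, the naive standard error can err either way.

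**Reading B: ever-detectable, no true difference in risk.** With beta-binomial results, let a = 0.03 × (1/ICC − 1) and b = 0.97 × (1/ICC − 1). Then P(ever detectable in m tests) = 1 − Γ(b+m)Γ(a+b) / [Γ(b)Γ(a+b+m)].

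| ICC | 4 tests | 8 tests | Spurious odds ratio |
|---|---|---|---|
| 0.1 | 10.0% | 16.6% | 1.79 |
| 0.3 | 7.8% | 11.1% | 1.48 |
| 0.5 | 6.1% | 7.9% | 1.31 |

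The two readings move in opposite directions with ICC: higher correlation worsens A and eases B. Neither error vanishes anywhere in the range shown.

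**Reading C: one result per woman in a fixed window.** There is no clustering, and ordinary logistic regression is adequate on that count. Whether a woman has a result in the window would still depend on standard-of-care testing.

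**Expected positives.** 150 women × 4 results × 3% = 18 positive results. This limits how large any corrected model can be.

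**The case against.** The strongest reply is that the article never says plasma is analysed at sample level. The sentence summarises a model family for several secondary outcomes and leaves the row structure to the full protocol or analysis plan. The milk analysis is explicitly about samples, with collection time as a covariate, so it needs a mixed model. Plasma as an outcome is not described that way, and Reading C fits the text. The authors evidently know when a random effect is called for.

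Much of this stands. A reader might infer that the plan commits itself to treating repeated plasma results as independent. The documents do not support that, because the unit of analysis is not given. A reader might also infer that the trigger above 50 copies/mL generates extra plasma rows. The article says the value triggers a visit but not that plasma is redrawn there. Finally, one might compute ever-detectable risk as 1 − 0.97^m, giving 11.5% for 4 tests and 21.6% for 8 (odds ratio 2.13). That assumes no within-woman correlation and cannot be set beside type I figures that assume 0.3 to 0.5.

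The reply does not remove the mismatch. A model class is named for this outcome, it differs from the one named for milk, and the article's own account shows that plasma results recur at a frequency the protocol does not fix. Of the three readings, only C suits the named model as far as clustering goes, and the text does not choose it.

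**Conclusion.** The point holds in a limited form. For this objective the stated model fits the available data poorly unless one result per woman is taken in a defined window. Otherwise, true type I error for woman-level factors is about 9% to 22% (per-result rows, 4 results per woman, ICC 0.1 to 0.5), or there is a spurious odds ratio of about 1.8 down to 1.3 (ever-detectable, 3% per test, 8 versus 4 tests, same ICC range). These are alternatives and do not add up. Their sizes rest on assumed test numbers, correlation and detection rate; only the direction follows from the article. No primary analysis, sample size or power figure is affected.

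**What to change.** State the unit of analysis for detectable plasma viral load. Analyse one plasma result per scheduled visit window, using mixed-effects logistic regression with a random intercept for woman and visit time as a covariate, or GEE with cluster-robust errors. Keep all visit-window rows: deleting repeats within one viremic episode would select on the outcome. With perhaps 18 positive results, use few covariates or penalisation, and enter site as a random effect or omit it. Twelve site terms on top of a random intercept may not be estimable. If ever-detectable is also reported, account for the number of tests or for follow-up time.

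The change is to analysis wording and needs no new data or visits. The cost is wider intervals and possible instability if positive results are few.
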